#### Procedure

2.2.11

Patients will be asked to attend the diabetes research center on 3 occasions. The first time sociodemographic questionnaire will be completed. Blood test will be taken at the first time and week 10 of the study by trained nurses. Twenty milliliter blood sample will be taken after an overnight fasting from the antecubital vein with patients in seated position. Prechilled tubes will be used to collect bloods. Blood sample that are collected will be centrifuged at 3000 rpm for 10 minutes at 4°C to obtain the serum and plasma. Blood sample that are collected will be stored at −80°C until further analysis. Serum inflammatory factors (IL-6, TNF-α, hsCRP, CD163); adhesive molecules (ICAM, VCAM, E-selectin); and ADMA, NO, and SIRT1 will be measured by using the specific kits and methods. Anthropometric measurements including weight, height, and WC will be performed by standard methods. Height will be measured using SECA stadiometer without shoes to the nearest 0.1 cm. Body weight will be measured without shoes and light clothing by using a SECA electronic scale (Seca, Hamburg, Germany) to the nearest 0.1 kg. WC in centimeter will be assessed midway between the lowest rib and the iliac crest using a nonstretchable tape measure. BMI will be calculated by dividing weight by the square of height. Twenty-four hours dietary recall questionnaire and IPAQ will also be completed.

#### Dietary intake assessment

2.2.12

Dietary intake will be estimated by using three 24-hour dietary recall at the beginning, middle, and at the end of the study. Patients will be asked to recall foods and drinks they consumed 24 hours before the interview by the investigator. Detailed descriptions such as time of the day, food ingredients, and portion size will be obtained by using Pictures of foods commonly consumed in Iran and common household measurement tools. Dietary intake will be analyzed with Nutritionist software version 4 (First Data Bank, San Bruno, CA).

#### Physical activity levels assessment

2.2.13

IPAQ will be administered to assess the physical activity level of the subjects. The IPAQ-SF form records 3 types of activities and time spent sitting. According to the IPAQ scoring protocol responses will be converted to metabolic equivalent task minutes per week (MET-min/wk): total minutes over the last 7 days spent on vigorous activity, moderate-intensity activity, and walking were multiplied by the energy cost of each activity: 8.0, 4.0, and 3.3 MET for vigorous, moderate, and walking, respectively.^[31]^

Figure 1 presents the overall contents of enrollment, interventions, and assessments. Moreover, the SPIRIT checklist is provided as an additional file.

The trial conduct is to be frequently audited by an assistant though an independent process.

#### Statistical analysis

2.2.14

The normality of the distribution of data will be assessed by using Shapiro-Wilk tests carried out on each parameter before analysis. By using “regression imputation” missing values will be replaced from a regression equation from observed data. By using intention-to-treat all randomized participants will be analyzed in their group. Independent *t* test will be used to evaluate the differences between the means of 2 independent groups with normal data and Mann-Whitney for non-normal data. In order to assess time-by-treatment interactions and time effects on all outcomes two way repeated-measures regression analysis will be used. A *P* value of <.05 will be considered as significant. All statistical analyses will be performed using SPSS version 21 (SPSS Inc, Chicago, IL).

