#### Sample size

2.2.2

Eighty patients with T2DM diagnosed by diabetes specialist physicians were recruited from Diabetes Research Center, Endocrinology and Metabolism Clinical Sciences Institute, Tehran University of Medical Sciences Tehran, Iran to detect a significant mean difference of hsCRP,^[28]^ 95% confidence level, and 80% power. Regarding a possible loss to follow-up, a safety margin of 20% was determined The patients were divided equally in the placebo and cardamom supplement groups. We started recruiting participants from Diabetes Research Center from November 20, 2016 to July 20, 2017 and by now we are collecting data from the questionnaires and blood sample tests. 
[figure not shown]

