#### Randomization

2.2.6

The participants will be randomly assigned into 2 groups green cardamom powder (n = 40) or rusk powder (n = 40). The permuted block randomization will be used in this study. Stratified randomization will be used to control BMI and gender distribution, those will be 25–29.9/30–34.9 kg/m^2^ for BMI and for gender, respectively. Randomization will be performed by an assistant and the intervention allocation will be blinded as A and B packages for investigators and patients.

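### Missing values are filled in once from an unspecified regression equation and analysed as observed: at 20% loss this either raises type I error to about 6–12% or shrinks the effect by about 20%

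*Protocol article*

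**What the plan says.** Section 2.2.14 (Statistical analysis) names regression imputation, under which "missing values will be replaced from a regression equation from observed data". The next sentence sets the analysis population: "By using intention-to-treat all randomized participants will be analyzed in their group". The completed data then go to the planned tests. The independent *t* "test will be used to evaluate the differences between the means of 2 independent groups with normal data", Mann-Whitney is used otherwise, and for time and time-by-treatment effects "two way repeated-measures regression analysis will be used". A P value "of <.05 will be considered as significant".

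The section does not say which predictors enter the equation, whether treatment arm is one of them, or whether a random residual is added. On the amount of loss, Section 2.2.2 (Sample size) says: "Regarding a possible loss to follow-up, a safety margin of 20% was determined".

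Two other places bear on who would have values imputed. The limitations listed after the abstract say that patients who do not cooperate to the end will be replaced by others. Section 2.4 (Ethical considerations) says that a person unable to continue supplementation will be excluded from the study.

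**The concern.** A value read off a fitted equation carries no residual scatter and adds no information beyond the data used to fit it. If it is then counted as a real observation, the analysis believes it has 40 per arm when it has fewer.

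What follows depends on whether the equation knows the arm:

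- **Arm in the equation, or one equation per arm.** Imputed values sit on their own arm's line. The effect estimate is sound, but the spread is too small and the sample size overstated, so the test rejects too often.
- **Arm left out.** Imputed values follow one common line. They dilute the between-group difference, while the test keeps roughly its nominal level.

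The rule is not limited to any outcome, so it applies to all twelve variables listed in Section 2.2.10.1, each tested at .05. In a trial of 80, a handful of imputed values per arm can change a conclusion.

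**Working it through.** **Inputs from the protocol.** 40 per arm (Section 2.2.6); a 20% margin for loss (Section 2.2.2); *t* test at .05 (Section 2.2.14; two-sided is assumed); bloods at the first visit and week 10 (Section 2.2.11), so a person lost before week 10 has only a baseline value for the blood markers.

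**Inputs assumed.** Normal data; values missing completely at random; correlation between baseline and week 10 from 0 to 0.8; outcome taken either as the week-10 value or as the change.

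**The plan's own figure.** Section 2.2.2 gives "95% confidence level, and 80% power" for a difference in hsCRP, but the readable text gives neither the difference nor the SD, so 80 can be neither reproduced nor refuted. The margin is consistent with it: 64 / (1 − 0.20) = 80. At 20% loss, 40 × 0.80 = 32 per arm are observed and 8 are imputed.

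**Arm in the equation, uninformative baseline (SD = 1).** Each imputed value equals the observed mean of its arm.
- True SE of the difference: √(2/32) = 0.250.
- Reported SE: the sum of squares comes from 32 values (31 degrees of freedom) but is divided by 39, and n is taken as 40, so √[2 × (31/39) / 40] = 0.199.
- Ratio: 0.199 / 0.250 ≈ 0.80.
- Type I error: 2 × [1 − Φ(1.96 × 0.80)] = 11.7%.

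**Arm omitted.** 32 of 40 values per arm carry the difference δ and 8 carry none, so the expected estimate is (32/40)δ = 0.80δ. For δ = 0.63 SD this is 0.504; for δ = 0.70 SD it is 0.56.

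**Simulation at 20% loss.** 40 per arm, 8 per arm missing, one deterministic fill from baseline, *t* test on all 80, 5,000 trials per setting (simulation error about 0.3 to 0.5 points). Entries are type I error in %; the ratio of reported to true SE is in brackets.

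| Outcome, correlation | Complete cases | Arm omitted | Arm in equation | Separate by arm |
|---|---|---|---|---|
| Week 10, 0 | 5.5 | 4.7 | 12.3 (0.79) | 11.1 (0.80) |
| Week 10, 0.5 | 5.4 | 4.6 | 9.5 (0.86) | 10.1 (0.83) |
| Week 10, 0.8 | 5.2 | 5.6 | 7.2 (0.91) | 6.3 (0.93) |
| Change, 0 | 5.2 | 5.3 | 8.2 (0.88) | 8.4 (0.89) |
| Change, 0.5 | 4.8 | 4.8 | 9.4 (0.85) | 9.2 (0.85) |
| Change, 0.8 | 5.3 | 5.1 | 11.1 (0.81) | 10.8 (0.81) |

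**Variants.**
- 10% loss, arm in the equation or separate by arm: 5.8–8.6%.
- 20% loss, arm in the equation plus one random residual: 6.4–10.9%.
- Mann-Whitney on change, arm in the equation, correlation 0.3–0.7: 9–13%.
- Arm omitted, correlation 0.5: a true 0.70 SD was estimated as 0.556 and a true 0.63 SD as 0.506, matching 0.80δ. In the 0.70 SD case power was 76%, against 78% for complete cases, so the harm is mainly to the estimate.
- Baseline-adjusted model on observed values only, correlation 0.3–0.7: type I error 4–5%.

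**The case against.** A reader might infer that the plan doubles the false-positive rate. The protocol does not support that as a general statement. Inflation needs arm in the equation, or separate equations by arm, and the protocol does not say so. Even then the range at 20% loss is about 1.3 to 2.5 times nominal, depending on an assumed correlation and on the form of the outcome. With a pooled equation the level holds and the error runs the other way, towards no effect. For the same reason it is too strong to say that every P value is wrong.

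A reader might also take 20% as the loss the trial expects. Section 2.2.2 calls it a safety margin for possible loss, and the strengths listed after the abstract claim minimal dropout. At 5% missing, type I error with arm in the equation was only about 5–6%.

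The number of imputed values is uncertain for another reason: if dropouts are replaced or excluded, fewer values are imputed than the intention-to-treat sentence implies.

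Finally, a full analysis plan may name the predictors. That would settle which harm occurs but would not remove it. The protocol states the method itself, and a single deterministic fill gives either false precision or a diluted effect. Adding one random residual softens the first without curing it. So the objections limit the size and certainty of the problem, and the criticism of the method stands.

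**Conclusion.** The concern holds in conditional form. A single regression fill treated as data is unsound whichever way the unstated equation is written. If loss reaches 20%, then with arm in the equation the standard error is about 10–20% too small (7–21% across all settings tried) and type I error is about 6–12%. With arm omitted, type I error stays near 5% and the effect is understated by about 20%. Both harms shrink as loss falls. The figures rest on normal data, missingness completely at random and the assumed correlations; informative dropout was not examined. Severity: should be fixed, but not fatal to the trial.

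**What to change.** In Section 2.2.14:

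1. Delete single regression imputation.
2. Make the main between-group comparison a baseline-adjusted model on the observed week-10 values of all randomised participants who have them, with arm, the outcome's baseline value, BMI stratum and gender. The last two are the stratification factors of Section 2.2.6. This is valid when missingness depends only on arm and these covariates.
3. Add multiple imputation as a sensitivity analysis, with a small model (arm, the outcome's baseline value, BMI stratum, gender), at least 20 sets, combined by Rubin's rules. Do not add the other week-10 markers: a dropout will usually lack them all, and about 32 observed patients per arm cannot support a long predictor list.
4. Reconcile the replacement statement (limitations after the abstract) and the exclusion statement (Section 2.4) with the intention-to-treat sentence, since together they determine who is followed and analysed.

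The cost is slightly wider confidence intervals and a little more analysis work. Step 2 replaces the planned *t* test and Mann-Whitney comparison, so it is more than a change of wording. Section 2.2.2 reports that data are still being collected, so the change can be made and dated before results are known.

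### Section 2.2.14 plans two unranked between-group tests, leaves open what the t test compares, and uses neither baseline nor strata as covariates, which costs precision

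*Protocol article*

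**What the plan says.** Section 2.2.14 (Statistical analysis) of the Protocol article gives two routes to a between-group comparison.

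- The first is an independent t test or its rank alternative: "test will be used to evaluate the differences between the means of 2 independent groups with normal data and Mann-Whitney for non-normal data". Normality is to be "assessed by using Shapiro-Wilk tests carried out on each parameter before analysis". The sentence names no outcome, time point or quantity (week-10 value or change).
- The second is a repeated-measures model: "In order to assess time-by-treatment interactions and time effects on all outcomes two way repeated-measures regression analysis will be used".

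One threshold covers everything: a P "value of <.05 will be considered as significant". The section does not rank the two analyses and names no covariate.

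Other sections bear on this:

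- Section 2.2.11 (Procedure) fixes the biomarker schedule: "Blood test will be taken at the first time and week 10 of the study".
- Section 2.2.10.1 (Primary outcome) defines the outcomes as changes.
- Section 2.1 (Objectives) speaks of comparing means between and within groups, before and after the intervention.
- Section 2.2.6 (Randomization) stratifies by BMI class and gender, with 40 patients per arm.

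**The concern.** Two questions arise.

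1. **Which analysis decides?** If the t test is run on week-10 values, it is a different test from the time-by-treatment test, and the two can disagree. The plan does not say which would then stand.
2. **Is the baseline well used?** It is collected for every blood marker, yet neither planned test enters it as a covariate. In a trial that lists small sample size among its own limitations, precision would be given up without any saving in data or patients.

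**Working it through.** **Inputs from the Protocol article.** There are 40 patients per arm (2.2.6). The design is set "to detect a significant mean difference of hsCRP", at "95% confidence level, and 80% power", with a 20% margin for loss (2.2.2). Blood is taken at two time points (2.2.11).

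**Assumed, because not in the documents.** The correlation r between baseline and week 10 is taken over 0.3 to 0.8. Variances at the two time points are taken as equal, and tests as two-sided.

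**The plan's own sample size.** The hsCRP difference and SD are not in the readable text (a figure is not shown), so 80 patients cannot be reproduced forward. Working backwards, 32/(1 − 0.20) = 40 per arm, and 33 × 1.20 = 39.6 also rounds to 40. With 32 per arm the detectable standardised difference is (1.96 + 0.84) × √(2/32) ≈ 0.70; with 33 it is about 0.69.

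**Equivalence.** With two time points and complete (or imputed) data, the time-by-treatment term is the difference between arms in mean change. Its test is a t test on change.

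**Relative variance of the treatment effect**, per unit SD:

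- week-10 t test: 1
- change (time-by-treatment) test: 2(1 − r)
- ANCOVA, week 10 adjusted for baseline: 1 − r²

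Inflation over ANCOVA is therefore 1/(1 − r²) for the week-10 test. For the change test it is 2(1 − r)/(1 − r²) = 2/(1 + r).

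| r | week-10 test vs ANCOVA | change test vs ANCOVA |
|---|---|---|
| 0.3 | 1/0.91 = 1.10 | 2/1.3 = 1.54 |
| 0.5 | 1/0.75 = 1.33 | 2/1.5 = 1.33 |
| 0.7 | 1/0.51 = 1.96 | 2/1.7 = 1.18 |
| 0.8 | 1/0.36 = 2.78 | 2/1.8 = 1.11 |

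Both ratios exceed 1 for every r strictly between 0 and 1.

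**Power under ANCOVA for an effect that has 80% under the comparator.** The expected z of 1.96 + 0.84 = 2.80 is multiplied by the square root of the inflation.

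- Against the change test: r = 0.3, 2.80 × √1.54 = 3.47, power about 94%; r = 0.5, 2.80 × √1.33 = 3.23, about 90%; r = 0.7, 2.80 × √1.18 = 3.04, about 86%.
- Against the week-10 test: about 84%, 90% and 98% at the same values of r.

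These are two separate comparisons, each with its own comparator set to 80%. They are not the ends of one uncertainty range.

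**Patients per arm for 80% power at 0.70 SD** (week-10 / change / ANCOVA): r = 0.3, 32 / 45 / 30; r = 0.5, 32 / 32 / 24; r = 0.7, 32 / 20 / 17.

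**Simulation check** (normal data, 40,000 trials per setting, 32 per arm, true effect 0.70 SD). Power for week-10 / change / ANCOVA was 78.6 / 64.5 / 81.5% at r = 0.3, 78.9 / 78.6 / 88.2% at r = 0.5, and 78.9 / 94.4 / 96.9% at r = 0.7. The pattern is that of the formulas, slightly lower throughout.

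**Two tests, by reading of the t test.**

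- *Week-10 values.* The two test statistics correlate at (1 − r)/√(2(1 − r)) = √((1 − r)/2), which is 0.59, 0.50 and 0.39 at r = 0.3, 0.5 and 0.7. If either significant result is claimed, the bivariate normal gives a per-outcome type I error of 8.9%, 9.1% and 9.4%. Simulation over r = 0.3 to 0.8 gives 8.6 to 9.8%. With a true effect of 0.70 SD, the tests disagree on significance in 21 to 28% of trials at 32 per arm and in 13 to 22% at 40 per arm.
- *Changes.* For normal data the two P values are identical, with no disagreement and no inflation. A discrepancy can remain only where Mann-Whitney replaces the t test; its size was not computed.

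**The case against.** The strongest case on the other side has four parts.

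1. **The two-test reading is an inference.** Only the regression sentence refers to all outcomes. The t test sentence says that it "will be used to evaluate the differences between the means of 2 independent groups" and no more, so it might be meant partly for baseline comparisons. Section 2.2.10.1 defines outcomes as changes, and on changes the two tests coincide for normal data. A reader might infer that every outcome is tested twice at .05 with a 9% error rate. The documents do not support that as a flat statement: it needs week-10 values in the t test and an either-test rule, and the plan states neither. This objection stands, and the 9% is conditional.
2. **Baseline is not ignored.** A reader might take the lack of a covariate to mean that the baseline goes unused or that the results would be biased. The time-by-treatment test subtracts each patient's baseline, and under randomisation both planned tests are valid. This also stands: the loss is one of efficiency.
3. **The equivalence is limited.** Section 2.2.11 mentions three visits and gives no schedule for blood pressure or anthropometry. The equivalence with a change test is therefore shown for blood markers only.
4. **A separate analysis plan might name covariates.** It might, and a missing covariate list alone would not be a finding. But section 2.2.14 commits to two specific unadjusted analyses and ranks neither, and nothing else in the article settles the choice. That part of the concern is not answered.

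**Conclusion.** The point holds in limited form. Section 2.2.14 does not say which analysis decides or what the t test compares, and neither planned test uses the measured baseline as a covariate.

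The firm part is precision. For blood markers, ANCOVA has lower variance than either planned test for any r strictly between 0 and 1. How much lower depends on r, which the documents do not give, and on equal variances. Against the change test the gain shrinks as r rises; against a week-10 test it grows. At r = 0.5 the two planned tests are equally inefficient, and 80% power becomes about 90%.

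The type I error of about 9% per outcome is a risk left open by the wording, not a property of the plan as written. The planned tests are individually valid; the defect is that they are unranked and less efficient than the data allow.

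**What to change.** In section 2.2.14, name one primary analysis per outcome: a linear model of the week-10 value on treatment arm, the baseline value of that outcome, and the randomisation strata (BMI class and gender). Log-transform skewed markers, at both time points. Report the adjusted difference between arms with its 95% CI.

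Label the t test/Mann-Whitney and the time-by-treatment test as supportive analyses that cannot change the conclusion, and state for the t test whether it compares week-10 values or changes.

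The cost is a rewording of one section, with no new measurements and no extra patients. Section 2.2.2 says that questionnaire and blood-test data were still being collected, so the choice should be recorded before results by arm are seen.

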### Data accessibility

2.3

The principal investigator will have access to the final trial dataset, and such access for other investigators is limited. The trial results will be presented only through the publication.

### Ethical considerations

2.4

This clinical trial is conducted after approval of the Ethics Committee of Tehran University of Medical Sciences and completion the informed consent. Whenever a person is unable to continue supplementation he/she will be excluded from the study.

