#### Inclusion criteria

2.2.4

Eighty patients within the age group of 30 to 50 years of either sex, body mass index (BMI) between 25 and 34.9 kg/m^2^, patients with T2DM who have been diagnosed with at least 2 years history, according to American Diabetes Association criteria, namely fasting serum glucose >7.0 mmol and last HbA1C value >7%, will be recruited from the regional outpatient diabetes care center. The patients should be on the stable doses of oral antidiabetic drugs throughout the study.

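### The intention-to-treat promise conflicts with the rules to exclude those who stop supplementation and to replace non-completers, so the analysis set is not fixed

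*Protocol article*

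**What the plan says.** Four statements in the protocol article bear on who is followed and analysed.

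- **Statistical analysis (2.2.14):** "By using intention-to-treat all randomized participants will be analyzed in their group". The same section says that "missing values will be replaced from a regression equation from observed data".
- **Ethical considerations (2.4):** "Whenever a person is unable to continue supplementation he/she will be excluded from the study".
- **Limitations list in the abstract:** patients who do not cooperate until the end of the study will be substituted by other patients. The article does not say how a substitute is assigned to an arm.
- **Sample size (2.2.2):** the 80 patients were chosen "to detect a significant mean difference of hsCRP" with "95% confidence level, and 80% power", and "Regarding a possible loss to follow-up, a safety margin of 20% was determined".

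Two further facts matter. Randomization (2.2.6) fixes 40 per arm by stratified permuted blocks. Procedure (2.2.11) places the blood draws at the first visit and week 10 only.

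**The concern.** Intention-to-treat needs two things: everyone randomised stays in the analysis set, and outcomes are sought from everyone, including those who stop the capsules. The exclusion rule undermines at least the second and, on one reading, the first. The replacement rule then restores the headcount with other people.

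Participants who stop may differ from those who continue, for example in tolerability or disease course, and the pattern may differ by arm. The article itself concedes that the aroma may reveal allocation, so equal stopping cannot be presumed. If stopping is both unequal and related to outcome, the between-group difference is biased for every outcome listed as primary. As the text stands, either an all-randomised analysis or a completers-plus-replacements analysis could be defended from it after the results are known.

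**Working it through.** **1. The plan's own figure.** The hsCRP difference and SD behind the 80 are not in the visible text (a figure is not shown), so the base sample size cannot be recomputed. The loss margin can be checked:

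- n/(1 − 0.20): 32/0.80 = 40 per arm, 80 in total.
- n × 1.20: 33 × 1.20 = 39.6, rounded up to 40 per arm, 80 in total.

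Both agree with 80, so the margin appears to sit inside the 80.

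**2. Is replacement needed for power?** With 20% loss, 80 × 0.80 = 64 are observed, 32 per arm. Two-sided 5% (sidedness assumed), 80% power, normal approximation: d = (1.96 + 0.84) × √(2/32) = 0.70 SD. If 32 per arm was the base, that is the design effect, and the planned power survives the planned loss without replacement.

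**3. The rules side by side.** If those who leave stay in the analysis, each replacement takes the number randomised above 80, against the 40 and 40 in Randomization. If the arms are to stay at 40, those who leave must stop being counted, against Statistical analysis. The article does not choose.

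**4. Does imputation repair this?** Someone excluded before week 10 has no post-baseline blood sample. A regression fitted to observed data is then fitted mainly to people who continued. It corrects only for the part of the difference between stoppers and continuers that the predictors explain.

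**5. Size of the bias under assumed inputs.** Let f be the fraction of an arm that is excluded and g the gap in mean outcome between those excluded and those who stay, in SD. Dropping the excluded shifts that arm's mean by f × g. With equal g, the between-arm bias is (f_cardamom − f_placebo) × g.

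- Equal f (for example 20% and 20%) or g = 0: bias 0.
- 20% against 5%, g = 0.5: 0.20 × 0.5 − 0.05 × 0.5 = 0.075 SD.
- 20% against 0%, g = 1.0: 0.20 × 1.0 = 0.20 SD.

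For scale, 40 fully observed per arm detect 0.63 SD with 80% power (noncentral t: 0.634), so the last two are 0.075/0.634 = 12% and 0.20/0.634 = 32% of that difference.

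**6. Second check, by simulation.** No true effect, 40 per arm, 3,000 runs. A participant stops when a normal variable correlated ρ with the outcome exceeds the cut-off giving the assumed stopping rate. A negative sign means lower values in the cardamom arm.

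| Stopping, cardamom / placebo | ρ | Bias, no replacement (SD) | Bias, replacement (SD) | Type I error, no replacement / replacement |
|---|---|---|---|---|
| 20% / 20% | 0.5 | 0.009 | 0.002 | 4.7% / 4.6% |
| 30% / 10% | 0 | −0.002 | 0.003 | 5.1% / 4.4% |
| 25% / 15% | 0.3 | −0.043 | −0.043 | 5.8% / 5.4% |
| 25% / 15% | 0.5 | −0.069 | −0.073 | 6.0% / 5.6% |
| 30% / 10% | 0.3 | −0.092 | −0.092 | 6.1% / 6.0% |
| 30% / 10% | 0.5 | −0.149 | −0.147 | 9.1% / 11.2% |

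A closed form agrees. The mean of those who stay is −ρ·φ(z)/(1 − f), with z the upper-f normal quantile and φ the normal density. For 30% against 10% and ρ = 0.5 the bias is −0.5 × (0.3477/0.70 − 0.1755/0.90) = −0.5 × (0.497 − 0.195) = −0.151 SD.

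Replacements here join the same arm and face the same stopping rule. They restore the headcount and leave the bias as it was.

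**The case against.** The best defence is that the only section defining the analysis set is Statistical analysis, and it names intention-to-treat with imputation. The exclusion sentence stands under Ethical considerations and may mean no more than withdrawal from the capsules or from follow-up. On one reading all the rules coexist: stoppers leave follow-up and are imputed in their own arm, added patients take the next block assignment, and everyone is analysed. The number randomised would then exceed 80, but no rule would be broken outright.

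Much of this stands, and it limits what can be claimed. A reader might infer that the trial has become a completer analysis; the article permits that but does not state it. A reader might also infer that replacements are not randomised. No allocation method is given, and the stratified blocks could supply one. Nor should the requirement "The patients should be on the stable doses of oral antidiabetic drugs throughout the study" be read as a rule for removing patients after randomisation: nothing in the article says that a dose change takes anyone out.

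The defence does not remove the conflict. The benign reading has to be constructed, since the article does not give it. Even under it, the outcomes of stoppers are not measured and are filled in mainly from people who continued.

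**Conclusion.** The point holds as a conflict between stated rules that leaves the analysis set open and can bias the result. It is more than detail left to an analysis plan, because the article states the conflicting rules itself. Confidence is high for the conflict and for the redundancy of replacement beside the 20% margin.

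Confidence in any particular size of bias is low. It runs from about zero, when stopping is equal between arms or unrelated to outcome, to roughly 0.1 to 0.2 SD under unequal, outcome-related stopping. The stopping rates, the outcome gap and the correlation are all assumptions; the article gives only an overall 20% planning margin and no split by arm. Because every primary outcome depends on who is analysed and the correction is cheap, the passages should be reconciled before the data are analysed.

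**What to change.** 1. Delete the replacement sentence from the limitations list.
2. Reword the sentence in Ethical considerations so that a participant who stops the capsules remains in follow-up, is invited to the week-10 measurement, and is analysed in the randomised group. This concerns follow-up and analysis only, not when a participant should stop.
3. Sample size gives recruitment dates ending in July 2017 and says that data are being collected, so replacements may already be enrolled. If so, analyse everyone randomised, including those who were replaced; state how replacements were allocated; and report separately any who were not allocated from the randomisation list.

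**Cost:** a wording change in two places, and some effort to bring those who stop back at week 10. Some of those visits may already be past, in which case only the analysis-side correction remains. The observed number may fall below 80, which the 20% margin was set to cover.
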